#### Sample size calculation

A sample size of 50 subjects will be required, 20 in each group, plus 10 in anticipation of future losses according to the recommendations for RCT pilot studies [95, 96].

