#### Statistical analysis

Statistical analysis will be performed with Statistical Package for the Social Sciences version 25.0 (SPSS Inc, Chicago, IL). The significance level will be 0.05 for all statistical analyses. Descriptive statistics, including frequency counts for categorical variables and measurements of central tendency and dispersion for continuous variables (standard deviation, 95% confidence interval) will be calculated to summarize the data.

The Shapiro-Wilk test will be used to determine the normality of the data.

General lineal models will be performed to compare the intervention effects [time (pre-intervention vs post-intervention vs follow-up 1 and 2 assessments) x group interaction] on the primary and secondary outcomes: severity of fatigue, functional status, self-efficacy, depression, anxiety and stress, quality of live, behavioral regulation in sport and perceived social support. It will be examined with analysis of variance (ANOVA) mixed model for repeated measures when normal distribution will be detected. A post hoc test will be used to locate the differences between the groups, if necessary. If data are not normally distributed, statistical analysis will be performed using non-parametric correspondent tests like Friedman test to compare the three moments involved and Wilcoxon test if statistics significance will be reached in previous Friedman test. In Wilcoxon test, type I error will be divided by the number of tests done.

For the aerobic capacity, strength, functional status post-COVID and feasibility outcomes, comparisons between-groups outcomes will be using t-tests for independent samples and Levene test for parametric data, or Mann-Whitney test U tests for non-parametric data. Chi-square and Fisher tests will be used of independence for categorical data. Finally, in the event of possible dropouts, analyses will be conducted as intention to treat.

Between- and within-group effect sizes using Cohen’s d or r for main outcomes will also be computed.

Chi square test for qualitative data and t-test or Mann-Whitney for normal or not normal data respectively will be used to check the comparability between the two groups at baseline.

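### The plan promises intention to treat, but the repeated-measures ANOVA and Friedman test named for fatigue use only patients with complete data, so as written the primary analysis is complete-case

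*Protocol article*

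**What the plan says.** The Statistical analysis section of the protocol article makes these statements, which have to be read together.

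- Software: "Statistical analysis will be performed with Statistical Package for the Social Sciences version 25.0".
- Model for the primary and most secondary outcomes: "General lineal models will be performed to compare the intervention effects [time (pre-intervention vs post-intervention vs follow-up 1 and 2 assessments) x group interaction". Time therefore has four levels.
- How that model is run: "It will be examined with analysis of variance (ANOVA) mixed model for repeated measures when normal distribution will be detected".
- Fallback for non-normal data: "non-parametric correspondent tests like Friedman test to compare the three moments involved and Wilcoxon test if statistics significance will be reached in previous Friedman test".
- Aerobic capacity, strength, post-COVID functional status and feasibility: "comparisons between-groups outcomes will be using t-tests for independent samples and Levene test for parametric data, or Mann-Whitney test U tests".
- Analysis population: "Finally, in the event of possible dropouts, analyses will be conducted as intention to treat".

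The section names no imputation or other missing-data method. Sample size calculation expects losses: "20 in each group, plus 10 in anticipation of future losses". According to Outcome measures, FSS is collected before and after the intervention and at three and six months. According to Procedure, the last two are collected by telephone.

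**The concern.** Intention to treat means that every randomised patient is analysed in the allocated arm. A general linear model repeated-measures ANOVA in SPSS deletes a patient who lacks any one of the repeated values, and Friedman requires complete blocks. An analyst who follows the text literally would therefore exclude the dropouts for whom the intention-to-treat sentence was written.

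Two things are at stake. The first is wasted data: a patient who attends the 12-week assessment but misses the six-month call disappears from the post-intervention comparison too, although that FSS was observed. The second is a mislabelled result: a complete-case estimate would be reported as intention to treat. If the more fatigued patients leave one format more often than the other, that estimate can be biased. Differential loss is plausible here, because adherence to each format is itself under study.

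**Working it through.** **Inputs from the protocol article.** 20 per group plus 10 for losses (Sample size calculation); 1:1 allocation (Allocation and blinding); four FSS visits (Outcome measures); SPSS 25, general linear model, Friedman (Statistical analysis).

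**Assumed inputs, not in the document.** Two-sided testing; per-visit missing rates of 5% to 20%; FSS SD 1.2; correlation 0.6 between any two visits; the dropout mechanism in step 5.

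**1. The plan's own figure.** 2 × 20 + 10 = 50. The implied loss is 10/50 = 20%, and 40/(1 − 0.20) = 50. The stated total reproduces.

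**2. Patients analysed.** If the anticipated 10 are lost, a complete-case analysis has 50 − 10 = 40, or 80% of those randomised. If instead a fraction m is missing independently at each of the three post-baseline visits, the number with all four values is 50 × (1 − m)³. A two-visit pre-post comparison keeps 50 × (1 − m).

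| m (assumed) | All four visits | Pre and post only |
|---|---|---|
| 5% | 42.9 | 47.5 |
| 10% | 36.5 | 45.0 |
| 15% | 30.7 | 42.5 |
| 20% | 25.6 | 40.0 |

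At m = 10%, 1 − 0.9³ = 27% of patients are deleted. The last column is what a pre-post Wilcoxon test would use.

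**3. Precision.** √(50/40) = 1.118, so standard errors are up to about 12% larger than with 50 patients. This is an upper limit: patients with missing visits contribute only part of the information, and those with no post-baseline value contribute almost none.

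**4. The same limit as a detectable difference.** For one two-group comparison with two-sided α = 0.05 and 80% power, d = (1.960 + 0.842) × √(2/n). With n = 20 per arm, d = 0.89 SD; with n = 25, d = 0.79 SD.

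**5. Possible bias (illustration, true difference zero).** A large simulation uses 10% random loss in the telerehabilitation arm and 30% in the booklet arm. The booklet arm's dropout probability is logistic in post-intervention FSS, with slope 0.5, 1.0 or 1.5 per SD. The completers' difference (telerehabilitation minus booklet) is:

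| Slope | Post, raw | Baseline | Post, change (raw − baseline) |
|---|---|---|---|
| 0.5 | 0.17 | 0.10 | 0.07 |
| 1.0 | 0.30 | 0.18 | 0.12 |
| 1.5 | 0.39 | 0.24 | 0.16 |

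The planned time by group interaction is a contrast of change, so the last column is the relevant one. The sign makes the booklet arm look better than it is. At three and six months the bias in change is about zero in this scenario.

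**6. Does the remedy remove it?** If the post-intervention FSS was observed before the patient left, using all observed values gives a difference of 0.00. If the patient left before that visit, the loss is not at random, and a baseline-adjusted post-intervention analysis is biased by 0.11, 0.20 and 0.26 points at the three slopes. That is more than the change contrast in step 5.

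**The case against.** **An unseen rule may reconcile the text.** ANOVA and Friedman are compatible with intention to treat once missing values are imputed, and a condensed article may leave the imputation rule to the full protocol or analysis plan. This stands in part. A reader might infer that the named procedures cannot deliver intention to treat at all, and the document does not support that. But the article does fix procedures that delete incomplete patients, so followed as written it conflicts with its own promise.

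**The text says mixed model.** If a linear mixed model was meant, incomplete patients are kept and the parametric route is sound. The general linear model wording, the ANOVA label, the Shapiro-Wilk check and Friedman as counterpart make a between-within ANOVA the likelier reading. The ambiguity would still need correcting.

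**Not every named test is affected.** A reader might infer that every test drops every patient with a missed visit. That is wrong. Wilcoxon loses a patient only when one of the two compared visits is missing, and the t-test and Mann-Whitney comparisons do not need four visits. Friedman is described for three time points although FSS has four, so which missed visit excludes a patient on that route is itself unclear.

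**The bias may be small or absent.** A reader might take the raw completers' difference of 0.30 points as the bias. The plan tests change, where the same scenario gives 0.12. A separate small simulation of the six-month change contrast, with equal correlations and booklet-arm dropout driven by post-treatment fatigue, found no detectable bias (0.017, standard error 0.012). This objection stands: bias depends on the mechanism, whereas the loss of patients does not.

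**It is a pilot, already sized for 40.** No power claim is broken, and 20 per group is the planned number after losses. That limits the consequence, but it does not justify calling a complete-case result intention to treat or discarding observed FSS values.

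**Conclusion.** The concern holds in a bounded form. For FSS and the other outcomes analysed over four visits, the named ANOVA and its Friedman fallback use only patients complete at all visits entered. Without imputation, the primary analysis is complete-case and does not match the intention-to-treat sentence.

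At the protocol's own anticipated loss, about 40 of 50 randomised patients are analysed. That follows from the stated figures, provided each of the 10 lost lacks at least one visit. The rise in standard errors is at most about 12%. The bias of 0.07 to 0.16 FSS points at post-intervention is conditional on the assumed SD, correlation and fatigue-dependent, unequal loss; it is not a prediction. The point rests on reading the model as a between-within ANOVA and on no imputation rule existing elsewhere.

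**What to change.** Replace the repeated-measures ANOVA with a likelihood-based linear mixed model (SPSS MIXED, REML). Use post-baseline FSS values as outcomes, with arm, visit, arm by visit and baseline FSS in the model. Include every randomised patient in the allocated arm with all available post-baseline visits, and define intention to treat in those terms. Apply the same form to the other four-visit outcomes, each with its own baseline. If Friedman or ANOVA is kept for any outcome, state which visits enter and how missing values are imputed.

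State that the model is valid under missing at random. It does not remove bias when patients leave before the post-intervention FSS is observed for reasons related to that value, so report losses by arm and visit.

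The cost is wording and slightly more analysis work. The software is already named and no new data are needed. Data management places the analysis after all data collection, so the change can be made before any analysis.

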#### Eligibility criteria

All potential participants will be informed before and will have to give their consent to participate in the study. The inclusion criteria will be: 1) post-COVID-19 patients discharged after more than 5 days hospitalized; 2) aged 18 to 75 years; 3) independent standing with or without technical aids; and 4) present a degree of fatigue ≥4 points in the FSS. The exclusion criteria will be: 1) having any other central and/or peripheral neurological disorders; 2) a previous history of rheumatic pathology or acute musculoskeletal injury; 3) patients with severe hypoxemia, defined as having a SaO2 less than 90% or a respiratory rate ≥30; 4) having any cardiac comorbidities or signs of cardiovascular instability as uncontrolled arrythmia, blood pressure and/or effort angina; 5) having any other contraindicated pathology for moderate-intensity aerobic or strength exercise; 6) a score ≤24 evaluated with the validated Spanish version of Mini-mental State Examination (MMSE-MEC) [33]; 7) no access to internet; and 8) to be unable to follow oral and written instructions in the Spanish language.

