### Outcome measures

#### Primary outcome: Fatigue

The primary outcome measure will be the fatigue, measured with the Fatigue Severity Scale (FSS). The FSS is a self-reported scale that allows assessing the severity of fatigue as a sense of physical tiredness, muscle weakness and lack of energy [38–40]. It is composed of 9 items with scores ranging from 1 = strongly disagree to 7 = strongly agree. The higher the number, the greater the severity of fatigue. The most common cut-off point is a mean score of 4 point, considering equal or more than 4 as severe fatigue [38, 41–45]. Three levels of severity will be considered: 4 = borderline fatigue; 5 = high fatigue; 6–7 = very high fatigue [44]. It has been shown to be reliable [38].

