## Discussion

This protocol describes a pilot and feasibility study to analyze the efficacy of an exercise and education therapeutic program using asynchronous telerehabilitation for post-COVID-19 patients. The aim of the pilot study will be to analyze if there are improvements in the participants´ level of fatigue and if these changes are maintained in the short (3 months) and medium term (6 months) and compare it with traditional home rehabilitation using a booklet. The secondary aim will be to analyze the feasibility of this pilot study.

Telerehabilitation is well accepted in terms of overall user experience, adherence, and satisfaction [94]. So, it represents a great opportunity for the treatment and monitoring of long-term patients. Currently, the large increase of COVID-19 cases during 2020 and 2021 has made telerehabilitation-based consultation a viable and reliable option in several pathologies. Scientific evidence shows how telerehabilitation is already effective in post-COVID-19 patients, as reported in the systematic review of da Silva et al. [97] where it was found that a physical programme using telerehabilitation can improve functional capacity, dyspnea and quality of life. Similarly, Dalbosco-Salas et al. [98], found that a group of post-COVID-19 patients undergo remote rehabilitation using synchronous telerehabilitation, achieved improvements in physical condition and quality of life. Although their model is on-line and there is no control group, the study shows positive results for post-COVID-19 patients in lower limb strength and quality of life. Furthermore, in most of the studies carried out in the acute and post-COVID-19 patients, the control group does not receive treatment.

Moreover, telerehabilitation has also shown to be effective in many other different conditions such as musculoskeletal pain, chronic obstructive pulmonary disease (COPD) or cardiovascular disease [99]. The study of Lewis et al. [100] showed that telerehabilitation is effective in COPD patients on multiple variables such as lower limb strength, fatigue, dyspnea, and anxiety, including improvements also in patient engagement and exercise progression. Similar results were obtained by Batalik et al. [101], who performed a study with asynchronous telerehabilitation in cardiac patients and showed also to be effective to improve the aerobic capacity assessed with the 200 meter fast-walk test.

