When telerehabilitation is compared to other formats, most of the studies about telerehabilitation reported clinical improvements in favor of telerehabilitation, but no statistically significant changes compared to other ways, which leads us to expect similar results in our study. Suso-Martí et al. [102] in their systematic review with meta-analysis, showed how telerehabilitation generated clinical improvements in physical condition variables in cardiorespiratory, musculoskeletal, and neurological patients, even comparable to conventional face-to-face rehabilitation. Other studies such as Dias et al. or Hansen et al. [103, 104] reported how telerehabilitation was not different to other interventions for physical function. The systematic review of Dias et al. [103] concluded that exercise via telerehabilitation can be an alternative to improve physical function and quality of live in persons with disabilities. Moreover, Hansen et al. [104] also found how telerehabilitation was similar to face-to-face rehabilitation in severe COPD patients to improve the aerobic capacity and the lower limb strength.

Regarding the psychosocial factors, several trials, such as ours, have implemented in their protocols a therapeutic education program together with the exercise program, with the aim of improving the emotional components by telerehabilitation [105]. These interventions seem to show better results than those based on isolated therapeutic exercise [103, 106]. However, although it seems that emotional factors can be improved with therapeutic education, it has no effect on decreasing the perception of fatigue [107]. In the cross-sectional study by Milani et al. [108] in adult population with a physical disability, it was observed that those patients who were able to undergo synchronous telerehabilitation via Skype had higher self-efficacy with respect to the control group. In addition, Hansen et al. [104] demonstrated improvements in the depression scale, compared to the group without telerehabilitation, measured with the HADS-D scale.

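### Because patients enter on FSS ≥4 and FSS is the primary outcome, the planned within-group Cohen's d on FSS can be non-zero with no true effect and should not be read as a programme effect

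*Protocol article*

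**What the plan says.** All references are to the protocol article.

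- **Eligibility criteria:** patients must "present a degree of fatigue ≥4 points in the FSS".
- **Primary outcome: Fatigue:** the same scale is the primary outcome. "It is composed of 9 items with scores ranging from 1 = strongly disagree to 7 = strongly agree", and the cut-off of 4 applies to the mean item score.
- **Intervention:** the exercise and education content is identical in the two arms; only the format differs.
- **Statistical analysis:** "General lineal models will be performed to compare the intervention effects" through the time-by-group interaction. The section then adds "Between- and within-group effect sizes using" Cohen's d or r for the main outcomes.
- **Discussion:** "The aim of the pilot study will be to analyze if there are improvements in the participants´ level of fatigue", whether the change is maintained, and how it compares with the booklet. On the comparison of formats, the authors cite earlier work that found "no statistically significant changes compared to other ways, which leads us to expect similar results in our study".

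The article does not say outright whether the FSS score used for entry is also the baseline score.

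- **Procedure:** a researcher confirms eligibility and then schedules the baseline assessment, which allows two separate measurements. The same section sets the starting exercise level from the pre-intervention FSS.
- **Intervention:** all three starting levels begin at 4 or higher, so a baseline below 4 has no level.
- **Outcome measures:** FSS is listed before and after the intervention and at three and six months, with no separate screening measurement.

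**The concern.** A score that must exceed a threshold for entry is, on average, partly high by chance. The next measurement in the same people falls back towards their usual level with no treatment effect at all. A before-after effect size on the selection variable includes that fall.

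In many randomised trials this is harmless because an untreated arm shows the same fall. Here both arms receive the same programme, so nothing in the design separates the programme's effect from the fall within an arm. The between-arm contrast answers a different question: whether one delivery format is better than the other.

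The authors expect little difference between formats, and part of their aim is to show that participants improve. If the trial turns out as they expect, a favourable conclusion would rest on within-arm change, and the within-group d is the figure planned to describe it.

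**Working it through.** **Plan's own figure.** There is none to reproduce for FSS. The article gives no FSS standard deviation, reliability coefficient or target effect. The only design figure is the sample size, 2 × 20 + 10 = 50.

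**Inputs.** From the article: entry cut-off 4, scale 1-7, same scale as outcome. Assumed: mean in unselected candidates 3.5-5, SD (σ) 1.25-1.5, test-retest reliability (ρ) 0.7-0.9, and no true change.

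**Formulas** (normal scores cut off at 4, entry score used as baseline):

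- a = (4 − mean)/σ and λ = φ(a)/(1 − Φ(a))
- expected fall at the next measurement = (1 − ρ) × σ × λ
- baseline SD after selection = σ × √(1 + aλ − λ²)
- null within-arm d on the baseline SD = fall / baseline SD

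**Case 1: the entry score is the baseline.**

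| Mean | σ | ρ | a | λ | Fall (points) | Baseline SD | Null d |
|---|---|---|---|---|---|---|---|
| 5 | 1.25 | 0.9 | −0.8 | 0.368 | 0.1 × 1.25 × 0.368 = 0.046 | 1.25 × 0.756 = 0.944 | 0.05 |
| 4 | 1.5 | 0.8 | 0 | 0.798 | 0.2 × 1.5 × 0.798 = 0.239 | 1.5 × 0.603 = 0.904 | 0.26 |
| 3.5 | 1.25 | 0.7 | 0.4 | 1.069 | 0.3 × 1.25 × 1.069 = 0.401 | 1.25 × 0.534 = 0.668 | 0.60 |

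A simulation with FSS held to 1-7 in steps of 1/9, over a somewhat wider SD range (1.2-1.8), agrees. Null d ran from 0.05 to 0.59 with median 0.20, and 17 of 36 combinations reached 0.2. Standardised on the average of the baseline and later SDs, it ran from 0.05 to 0.46. On the SD of change, it ran from 0.08 to 0.43.

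**Anchoring to the article.** The Introduction gives fatigue in 46-53% of post-COVID cases. If that share also passes FSS ≥4 (an assumption), null d on the baseline SD is 0.12-0.15 at ρ = 0.9, 0.24-0.30 at ρ = 0.8 and 0.37-0.44 at ρ = 0.7. At 50% passing, for example, λ divided by the SD ratio is 0.798/0.603 = 1.32, so ρ = 0.8 gives 0.2 × 1.32 = 0.26.

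**Case 2: separate screening and baseline scores, both required to be at least 4.** Simulated over the same means and reliabilities, null d is 0.03-0.36.

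**Case 3: entry on a separate score, baseline a fresh measurement with independent error and no cut-off of its own.** The regression happens before baseline, and the expected fall and d are 0.00.

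**Role of the restricted SD.** With 46-53% passing, the cut-off leaves 58-62% of the unselected SD, so any change is divided by a smaller number and d is multiplied by about 1.6-1.7 (1/0.62 to 1/0.58). If the change is zero, d stays zero.

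**The case against.** The strongest reply is that the efficacy comparison is untouched. Regression to the mean is equal in expectation in two randomised arms, so the time-by-group contrast is not biased by it, and the effect sizes are an addition to that test. This stands. A reader might infer that the entry rule distorts the comparison of the two formats; the documents do not support that.

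Three other strong readings are also unsupported.

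- A reader might infer that an ineffective programme would necessarily show a small-to-medium effect in each arm. That depends on a mean, SD and reliability that the article does not give, and under plausible values the null d can be trivial.
- A reader might blame the restricted baseline SD for creating an effect. It only magnifies a change that is already there, and it does not act in that way if d is standardised on the SD of change.
- A reader might treat the unnamed standard deviation for Cohen's d as a defect. That detail is commonly left to a statistical analysis plan, which is not shown here.

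It can also be said that eligibility is checked before the baseline visit, so the regression may be over by then. That is possible, and it is why the range includes zero. But the starting levels and the list of FSS assessments favour a baseline that is itself at least 4, in which case some regression remains.

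What survives is narrower than any of these readings: a within-arm figure is planned on the selection variable, no arm is free of the programme, and the article's stated aim and expectation give that figure weight.

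**Conclusion.** The point holds as a limit on interpretation. A within-group d on FSS cannot be read as a programme effect, because its expected value under no effect need not be zero. Its size is uncertain. On the assumed candidate distribution it is about 0.05-0.6 on the baseline SD if entry and baseline are one measurement, about 0.03-0.36 if both of two scores must be at least 4, and 0 if the baseline is fresh and unselected. The article's text favours one of the first two cases but does not settle it.

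The range rests on normally distributed scores, independent measurement errors, and the assumed mean, SD and reliability. It does not extend to the between-arm contrast. The consequence is for what the trial may conclude: if the formats perform alike, as the authors expect, within-arm d alone would not show that fatigue improved because of the programme.

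**What to change.** State that the efficacy conclusion on FSS rests on the baseline-adjusted difference between arms, in FSS points, with its 95% CI. Drop the within-group d for FSS, or report it labelled as uncontrolled change that includes regression to the mean and not as a programme effect. A sentence saying whether the entry FSS is also the baseline FSS would tell readers which of the three cases applies.

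All of this uses data already planned for collection. The cost is slightly more analysis, some wording, and less favourable within-arm statements.
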